## Introduction

Hyperthyroidism is a common condition affecting 3% of women and 0.3% of men in the UK.^1^ Common clinical features indicating hyperthyroidism include weight loss, heat intolerance, tremor, palpitations and anxiety.^2^ Treatment is critical to minimise complications including atrial fibrillation and stroke that contribute to the observed 20% increase in mortality.^3^

There are three treatment options: antithyroid drugs (ATDs), radioactive iodine (I-131, radioiodine) or surgical, either as a total or hemithyroidectomy. ATDs are associated with a high rate of relapse (30%–70%),^4^ while treatment with radioiodine or thyroidectomy leads to the development of hypothyroidism, requiring lifelong levothyroxine replacement, which is seen in 80% of patients administered radioiodine and up to 100% undergoing thyroidectomy. Guidance recommends discussion of all three options with the patient.^5 6^ There is insufficient evidence to recommend one treatment over the others, although some studies indicate differences in cardiac events and mortality between the treatment modalities.^7 8^

Weight gain following various treatments for hyperthyroidism has been described.^9 10^ Clinicians commonly assume that the observed weight gain is a simple regain of weight lost prior to the initiation of treatment. However, an analysis of 1373 patients with hyperthyroidism has demonstrated a higher prevalence of obesity at 3 years of follow-up when compared with the age-matched and sex-matched background population (37% vs 26% in men, p<0.001; 32% vs 26% in women, p<0.001).^11^ These findings suggest excess weight gain beyond patients’ premorbid weight (weight overshoot). Additionally, the study showed significant differences in final weight gain compared with baseline between those treated with ATDs (5.4 kg, 95% CI 4.8 to 6.0) and those who received radioiodine but did not develop hypothyroidism (5.1 kg, 95% CI 4.3 to 6.1) when compared with those treated with radioiodine who developed subsequent hypothyroidism (7.1 kg, 95% CI 6.6 to 7.7). The extent of weight change in patients treated with thyroidectomy was not evaluated.

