### Outcomes

The primary outcome is weight change (in kilogram) during and following the treatment for hyperthyroidism, as well as prevalence of obesity following the treatment. The secondary outcomes include cardiometabolic events and mortality as presented in table 1.

**Table 1 T1:** Secondary outcomes and their data sources

Secondary outcome	Source
MACE (cardiovascular death, nonfatal myocardial infarction or non-fatal stroke)	HES
Type 2 diabetes mellitus	CPRD
Congestive heart failure	HES
Ischaemic heart disease	HES
Stroke and transient ischaemic attack	HES
Cardiovascular mortality	ONS
All-cause mortality	ONS

CPRD, Clinical Practice Research Database; HES, Health Episode Statistics; MACE, major adverse cardiovascular event; ONS, Office for National Statistics.

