Additionally, in order to allow for the fact that patients may die, and their weight trajectories will be subject to informative dropout due to death, we will model weight changes using a flexible joint modelling approach.^22^ Effectively, the analysis of weight history will combine three techniques: (1) complete-case analysis (including only patients with at least one, either quantitative or qualitative, weight status code in each of the phases); (2) imputation of weight where qualitative codes are present; and (3) joint modelling to incorporate the informative missingness due to death. To check the sensitivity of the correctly specified imputation model, a fully Bayesian approach that jointly imputes missing values and estimates the parameters of the longitudinal model will also be conducted.^23–25^ Weight in all three treatment groups will be modelled simultaneously; the ATD group will be used as the reference group. Any marginal pairwise comparisons will be corrected for multiple testing by applying Bonferroni correction.

Further, the sensitivity to death and to missed treatment coding will be checked. During our meetings with the patients, we were informed that weight changes are important but are not of the utmost priority. In the face of death or any serious illness, weight maintenance loses its importance. Hence, our interest in weight changes in an immortal cohort, and thus, we would like to model weight in patients in such health that allows them to survive to the end of the study. Patients who died during the study will be excluded.

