The estimation of propensity weights will be conducted by the method proposed by McCaffrey *et al*.^31 32^ The appropriateness of IPW analysis will be assessed by checking the overlap (positivity assumption). According to the positivity assumption, each patient should have a non-zero probability of being indicated to each treatment category. Lack of overlap in the distribution of observed pretreatment characteristics between groups receiving different treatment indicates the positivity assumption is violated. This overlap will be checked visually. If poor overlap is identified, we will use Rubin’s trimming method,^33^ allowing discarding non-overlapping cases.

Further, pairwise balance in the distribution of all included variables between the three treatment groups will be tested with linear regression for continuous variables, logistic regression for binary and multinomial logistic regression for nominal variables. The analysis will be done without and with adjustments. The propensity weights will be considered balanced if there are no statistically significant (p<0.05) differences between the likelihood of receiving a different type of treatment. If imbalances remain after weighting, a doubly robust estimation approach will be applied^32^; that is, the imbalanced variables will be added to the model.

While IPW will adjust for confounding at baseline, other time-varying adjustments will be applied to correct for the events between the baseline and the outcome. The proposed covariates are treatment with levothyroxine for developed hypothyroidism, log TSH levels and informative observations of number of GP visits in a unit of time.

Incidence rate ratios of outcomes will be calculated with Poisson regression and modelled adjusting for time-varying covariates as listed further. Time-to-event analysis with adjustments will be modelled. The appropriate model will be applied, depending on the proportional hazard assumption’s results: if the assumption holds—Cox proportional hazard regression will be used; if it is violated, alternative techniques such as time-varying measures in extended Cox models will be applied.

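### Holm's step-down rule could replace Bonferroni for the pairwise weight comparisons: same family-wise error control, never fewer rejections

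*Protocol article*

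**What the plan says.** The Outcomes section of the protocol article states: "The primary outcome is weight change (in kilogram) during and following the treatment for hyperthyroidism", with post-treatment obesity prevalence alongside it. Under Natural history of weight changes, weight is modelled over three stages (premorbid, treatment, post-treatment). The same section states: "Weight in all three treatment groups will be modelled simultaneously; the ATD group will be used as the reference group". The multiplicity rule follows: "Any marginal pairwise comparisons will be corrected for multiple testing by applying Bonferroni correction".

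The procedure is therefore named in the article and not left open. The article does not fix the family-wise level for these comparisons, how many comparisons are in the family, or the arm sizes. The only 0.05 threshold in its methods concerns covariate balance after propensity weighting, "no statistically significant (p<0.05) differences between the likelihood of receiving a different type of treatment", and does not govern the weight analysis.

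**The concern.** Bonferroni tests every comparison at the family-wise level divided by the number of comparisons, whatever the other comparisons show. Holm starts at that same threshold for the smallest p-value and relaxes it after each rejection. Neither rule needs an assumption about the dependence between the tests, and both control the family-wise error strongly. For hypothesis tests, then, Bonferroni gives up power with no gain in error control.

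What is at stake is the second and third comparisons on the primary outcome, particularly any that involve a small arm. The Introduction notes that the earlier study did not evaluate weight change after thyroidectomy, so the pairs that include thyroidectomy are where the new evidence would come from.

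**Working it through.** The article states no power, sample size or level for the weight comparisons, so there is no figure of its own to reproduce. What follows is illustration under stated assumptions.

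**Inputs**
- Three groups with antithyroid drugs (ATD) as reference (Natural history of weight changes): three pairs if all are compared, two if only the comparisons with ATD are made. The article does not say which.
- Family-wise level 5%, two-sided: assumption.
- Starting point of 80% power for one pair at 5%: assumption.
- Earlier study of 1373 patients (Introduction): weight gain 5.4 kg (95% CI 4.8 to 6.0) on ATD, and 7.1 kg (6.6 to 7.7) after radioiodine with later hypothyroidism.

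**Thresholds**
- Bonferroni, three comparisons: 0.05/3 = 0.0167 for each, critical z 2.394. Two comparisons: 0.05/2 = 0.025, critical z 2.241. No correction: z 1.960.
- Holm, three comparisons: 0.05/3, then 0.05/2, then 0.05, taking the p-values from smallest to largest.

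**Power of one pair.** Power = Φ(δ − z_crit), with δ = 1.960 + 0.842 = 2.802 for 80% power at 5%.
- Two comparisons: Φ(2.802 − 2.241) = 71.2%.
- Three comparisons: Φ(2.802 − 2.394) = 65.8%.
- Under Holm, if the other comparisons are clearly significant, the pair is tested at 5% and has the full 80%. This is the best case.

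**Simulation.** Three normal means with known variance, equal groups, 400,000 replicates, three pairs, effects set so that Bonferroni has 80% power per true (or adjacent) pair:

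| Scenario | Quantity | Bonferroni | Holm |
|---|---|---|---|
| No differences | Family-wise error | 4.4% | 4.4% |
| One group differs | Power per true pair | 80.0% | 82.9% |
| One group differs | Both true differences found | 68.7% | 74.4% |
| One group differs | At least one true difference found | 91.4% | 91.4% |
| One group differs | Error on the one true null | 1.7% | 3.7% |
| Equal steps between all three | Power per adjacent pair | 79.8% | 89.6% |
| Equal steps between all three | All three differences found | 60.6% | 79.6% |

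Holm's family-wise error stays within 5%. Its gain is entirely in the later comparisons.

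**Size with the earlier study's figures**, taking its intervals at face value:
- SE on ATD = (6.0 − 4.8)/3.92 = 0.306; SE after radioiodine with hypothyroidism = (7.7 − 6.6)/3.92 = 0.281.
- Difference = 7.1 − 5.4 = 1.7 kg; SE = √(0.306² + 0.281²) = 0.415; z = 4.09.
- Power at 0.0167: Φ(4.09 − 2.394) = 95.5%. At 0.025: Φ(4.09 − 2.241) = 96.8%. At 0.05: Φ(4.09 − 1.960) = 98.4%.
- The most that could be recovered is 98.4 − 95.5 = 2.9 points.

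**A further gain, for one contrast only.** Suppose each group contributes one prespecified weight-change contrast, such as premorbid to post-treatment. If any two groups differ on it, at most one of the three pairwise nulls can be true. A 2-df test that the contrast is equal across groups, followed by each pair at the full level, is then a closed test with strong control. In the one-group-differs scenario it gives 87.8% power per true pair and 82.8% for both, with error on the true null of 5.0%.

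**The case against.** **Bonferroni is a legitimate choice.** It is valid, conservative, prespecified and contradicts nothing else in the article. This stands, and it makes the point one of efficiency.

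**The loss is not tied to this cohort.** The 5% level, the number of comparisons and the 80% starting power are all assumptions, and the article describes its sample as large. This also stands. A reader might infer from the drop from 80% to 66% that the primary comparison is underpowered. The documents do not support that: no arm sizes are given, and the earlier study's difference implies a loss of about 3 points.

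**Bonferroni supplies matching simultaneous intervals.** Holm does not do so simply. In a study meant to quantify weight gain for patients, intervals matter as much as p-values. With Holm, an unadjusted 95% CI can exclude zero while the adjusted p-value is not significant, and a Bonferroni interval can include zero while Holm rejects. This is a real cost, and labelling the intervals limits it.

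**An overall gate does not fit the model as described.** A reader might infer that, with three groups, one overall 2-df test of treatment would free every pair to be tested at 5%. The article does not support that in general. Its target is change in weight over several stages, so differences between treatments are treatment-by-stage contrasts. A 2-df main effect of treatment would mix in premorbid weight differences. Across several stages, more than one pairwise null can be true even when some groups differ. The shortcut holds for one prespecified contrast per group at a time.

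**Conclusion.** The point holds as a low-severity improvement. The article fixes a single-step rule for the pairwise comparisons on its primary outcome, and Holm gives the same family-wise protection under the same assumptions and never rejects less. That ordering holds at any family-wise level and for any number of comparisons.

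At an assumed 5% two-sided level, the most that Holm can return to a pair with 80% power at 5% is about 14 points with three comparisons (66% to 80%) or 9 points with two (71% to 80%). It adds nothing to the chance of at least one rejection. The actual loss here cannot be calculated from the article and may be only a few points. It would be largest for comparisons with a small arm. Nothing in the article makes the planned Bonferroni analysis invalid.

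**What to change.** Under Natural history of weight changes, replace the Bonferroni correction with the Holm correction, applied across all pairwise weight comparisons actually made, counting both pairs and stages. State the family-wise level and list the comparisons in the family.

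Optionally, where a single prespecified weight-change contrast per group is compared, test its equality across the three groups on 2 df at the family-wise level and, if that rejects, test each pair at the full level. Use this instead of Holm for that contrast only, and do not extend it to several stages at once.

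Report Holm-adjusted p-values beside 95% confidence intervals labelled as unadjusted, or beside Bonferroni intervals, and note that intervals and tests may occasionally disagree.

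The cost is a sentence or two of text. No new data or model is needed. The one loss is the exact match between tests and simple simultaneous intervals. If the investigators value that match more than the extra power, keeping Bonferroni and saying why is defensible.

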#### Prevalence of obesity

Post-treatment obesity in patients will be defined as ≥30 kg/m^2^, in line with the WHO definition,^26^ or identified from the Read codes when quantitative values are not available. The prevalence of obesity will be assessed in the entire cohort and stratified by the treatment group.

The post-treatment BMI will be compared with those in the background population (Health Survey for England). Two measures of effect will be investigated: (1) difference in overall BMI (kg/m^2^) and (2) difference in proportions of obesity. The effects will be tested with linear regression and logistic regression, respectively, in reference to the background population. The analyses will be adjusted for age and stratified by sex. Only complete case analysis will be conducted.

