### Aims and objectives

The overall aim of this study was to investigate the risks of gaining weight and developing obesity, developing cardiometabolic conditions or death following treatment for hyperthyroidism and to compare these risks between the three treatment modalities.

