#### Primary objective

The primary aim of this study was to assess the effect of type of treatment on weight changes during and after therapy for hyperthyroidism. The post-treatment prevalence of obesity will also be evaluated and compared with that of the general population.

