### Data sources

CPRD collects and anonymises patient electronic health record data from a network of general practitioner (GP) practices across the UK.^19^ Although the records in the database cover all four UK countries, HES-linkable records are limited to those from England only. Two HES datasets will be used: HES outpatient and HES admitted patient care. Linkage to HES databases is required to obtain the data, which may be missing from the GP records on non-medical treatment for hyperthyroidism (radioactive iodine and thyroidectomy). Additionally, data on MACEs will also be sourced from HES, as such events are typically being treated in the hospital setting.

Linkage to social data is required to adjust the analysis for socioeconomic status, which is a known risk factor for obesity and increased mortality. This will be obtained as the Index of Multiple Deprivation (IMD). Linkage to Office of National Statistics data is required to get access to the date of death and cause of death. Prevalence of post-treatment obesity will be compared with the background population sourced from Health Survey for England, a yearly survey monitoring trends in the nation’s health and care.

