### Data analysis

#### Natural history of weight changes

Descriptive statistics will provide summaries about the sample and weight as the outcome measure.

The natural history of weight changes will be modelled longitudinally. The model will estimate the weight (kilogram) over three stages: premorbid, duration of treatment and post-treatment. Premorbid weight is defined as body weight recorded at least 3 months before diagnosis or treatment initiation (whichever comes first). The treatment phase will start from the time of diagnosis or the first prescribed dose or procedure and will last until 3 months after the last recorded date of treatment. Any weight recoded thereafter will be considered as post-treatment.

Only patients having at least one weight record (quantitative or qualitative) in each of the three phases of the condition (premorbid, treatment and post-treatment) will be included in the natural history of weight analysis. The extent of missing data will be reported. As with any real-world data, we anticipate a relatively high proportion of intermittent missing weight data. This missingness can be assumed to be missing at random conditional on other covariates.^20^ Hence, the missing values will be imputed using the multiple imputation by chained equations (MACE).^21^ To improve precision of the imputation, the existing qualitative information from Read codes stating the direction of change (eg, ‘weight increasing (1622.00)’) or body mass index (BMI) status (eg, ‘overweight (22AA.00)’) together with other demographic and clinical covariate data will be entered into the imputation regression model.

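### The obesity comparison with the general population is made only after treatment, so it cannot separate obesity that predates hyperthyroidism from obesity developed after treatment

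*Protocol article*

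**What the plan says.** The overall aim (Aims and objectives) is to "investigate the risks of gaining weight and developing obesity" following treatment, among other risks, and to compare these risks between the three treatments. The abstract's Ethics and dissemination paragraph also promises knowledge on the risk of developing obesity.

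The general-population comparison that serves this aim is tied to one time point wherever it is described:

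- Primary objective: "The post-treatment prevalence of obesity will also be evaluated and compared with that of the general population".
- Data sources: "Prevalence of post-treatment obesity will be compared with the background population sourced from Health Survey for England".
- Prevalence of obesity: "The post-treatment BMI will be compared with those in the background population (Health Survey for England".

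The last section also fixes the estimands and the model. "Two measures of effect will be investigated: (1) difference in overall BMI (kg/m^2^) and (2) difference in proportions of obesity". These use linear and logistic regression respectively, on complete cases. "The analyses will be adjusted for age and stratified by sex". No premorbid BMI term and no premorbid contrast with the survey appears.

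Premorbid data are in the plan, but elsewhere. Under Natural history of weight changes, "Premorbid weight is defined as body weight recorded at least 3 months before diagnosis or treatment initiation", whichever comes first. That weight enters a three-stage longitudinal model in kilograms, fitted only in patients with a weight record in each stage.

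**The concern.** Prevalence at one time point counts everyone who is obese then, whenever they became so. Developing obesity is a change of state and needs the earlier state as well. A gap between the treated cohort and the survey measures acquired obesity only if the cohort resembled the general population before the illness. The planned analysis neither checks nor adjusts for that.

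The Introduction shows how easily the step is taken. It reports a follow-up contrast with the background population from an earlier study and comments: "These findings suggest excess weight gain beyond patients’ premorbid weight (weight overshoot". The obesity analysis planned here has the same structure and invites the same reading.

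What is at stake is the meaning of one component of the primary outcome. If the cohort was already heavier than the population before the illness, a positive gap would overstate what followed treatment; if it was leaner, the gap would understate it. The breakdown by treatment group has the same weakness. BMI status is a proposed covariate for treatment assignment in the propensity model, but that weighting is specified only for the cardiometabolic outcomes and mortality. Crude post-treatment prevalence by group may therefore partly reflect who was obese when treated.

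**Working it through.** The article states no figure for this analysis, so there is none to reproduce. The check is a decomposition, illustrated with the earlier study's prevalences.

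**Inputs from the Introduction.** Men: 37% post-treatment, 26% background. Women: 32% and 26%.

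**Assumption.** Premorbid prevalence is not given. It is varied from the background value to the post-treatment value. Background prevalence is held fixed between the two time points, for illustration only.

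**Formula.** Post-treatment excess = premorbid excess + change since premorbid, so

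change = (post − background) − (premorbid − background).

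On the odds scale the planned contrast is odds(post)/odds(background), and the change is odds(post)/odds(premorbid).

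**Planned contrast.**

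- Men: 37 − 26 = 11 points; OR = (0.37/0.63)/(0.26/0.74) = 1.67.
- Women: 32 − 26 = 6 points; OR = (0.32/0.68)/(0.26/0.74) = 1.34.

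**Change since premorbid.**

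| Sex | Assumed premorbid prevalence | Premorbid excess | Change, points | Change, OR |
|---|---|---|---|---|
| Men | 26% | 0 | 11 | 1.67 |
| Men | 31.5% | 5.5 | 5.5 | 1.28 |
| Men | 37% | 11 | 0 | 1.00 |
| Women | 26% | 0 | 6 | 1.34 |
| Women | 29% | 3 | 3 | 1.15 |
| Women | 32% | 6 | 0 | 1.00 |

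Within each sex the planned output is the same in every row; only the last two columns differ, and the plan does not estimate them. If premorbid prevalence lay below the background value, the change would exceed the post-treatment gap. With a gap of zero, the change equals minus the premorbid excess.

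**Does another planned analysis supply the missing element?** The three-stage weight model uses each patient's own premorbid weight and estimates the change to post-treatment, so it covers overshoot in kilograms. It leaves two things open. It does not say how many patients crossed the obesity threshold. It has no population reference, so it cannot set the change against the gain that people of the same age and sex had over the same calendar years. Nothing under Prevalence of obesity links the two analyses.

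**The case against.** The strongest reply is that the analysis does what its objective says. The Primary objective asks for post-treatment prevalence against the general population, and the article's list of strengths presents this as contextualisation. Pre-existing cases belong in a prevalence, and no analysis section commits to reporting the survey gap as overshoot. The Introduction's remark is a hedged comment on an earlier study. All of this stands: the contrast is correctly labelled and valid as a description. It does not meet the broader aim of the risk of developing obesity, which no specified analysis estimates on the obesity scale.

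The second reply is that overshoot has its own analysis. That also stands, and it rules out a stronger reading. A reader might infer that a null survey gap would hide real overshoot and that patients would be given the wrong message either way. The documents do not support this, because the within-patient model is part of the primary outcome and would show a gain above premorbid weight whatever the survey gap was.

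A reader might also convert the earlier study's gaps to kilograms and conclude that a premorbid excess is likely. The shift from 26% to 37% is 0.311 SD and from 26% to 32% is 0.176 SD. With an assumed normal BMI, SD 4.5 to 6 kg/m² and heights of 1.75 m and 1.62 m, these give 4.3 to 5.7 kg in men and 2.1 to 2.8 kg in women. The arithmetic holds, but setting it beside the quoted mean gains of 5.1 to 7.1 kg proves nothing. Those gains are by treatment, not by sex, and the SDs and heights are not in the article.

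Finally, an article condenses the full protocol, and further estimates may sit there. That is possible, but this section states its comparison, effect measures, models and adjustment, and it is that stated choice which is at issue.

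**Conclusion.** The point holds in a limited form. The obesity component of the primary outcome cannot distinguish obesity present before hyperthyroidism from obesity developed after treatment, although the latter is a stated aim. Overshoot in kilograms is covered by the weight model; obesity status and a population reference for the change are not.

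The size of the problem cannot be known from the document. The ranges of 0 to 11 points in men and 0 to 6 in women are illustrative: they come from an earlier study and rest on premorbid prevalence lying between the background and post-treatment values. They show that the contrast does not identify the acquired part, not that a premorbid excess exists.

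This should be fixed. It is a cheap improvement to one component and no reason to doubt the primary weight analysis.

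**What to change.** In the Prevalence of obesity section:

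1. Among patients with both a premorbid and a post-treatment BMI, compare each with Health Survey for England data of the matching calendar year, age and sex. Report the change in the gap for mean BMI and for the proportion obese.
2. Report new obesity among patients not obese premorbidly, by treatment group.
3. Keep the post-treatment-only contrast as descriptive. State that it is not to be read alone as overshoot or as obesity developed after treatment.
4. Add a sensitivity analysis using only premorbid weights recorded well before diagnosis. Weights near the 3-month limit may already reflect illness-related loss, which would lower the premorbid gap and inflate the apparent change.

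Premorbid weights and the survey are already in the plan, so no new kind of data source is needed. It is still more than one extra regression: survey data must be matched at two calendar times, and the survey years must reach back to the premorbid records, some of which will predate 1996. Requiring BMI in both phases reduces precision and may select patients who are weighed more often, so the paired subset should be described against the full cohort.

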**Methods and analysis:**

The study will establish the natural history of weight change in hyperthyroidism, investigate the risk of obesity and risks of cardiometabolic conditions and death relative to the treatment. The data on patients diagnosed with hyperthyroidism between 1 January 1996 and 31 December 2015 will come from Clinical Practice Research Datalink linked to Hospital Episode Statistics and Office of National Statistics Death Registry. The weight changes will be modelled using a flexible joint modelling, accounting for mortality. Obesity prevalence in the general population will be sourced from Health Survey for England and compared with the post-treatment prevalence of obesity in patients with hyperthyroidism. The incidence and time-to-event of major adverse cardiovascular events, other cardiometabolic outcomes and mortality will be compared between the treatments using the inverse propensity weighting model. Incidence rate ratios of outcomes will be modelled with Poisson regression. Time to event will be analysed using Cox proportional hazards model. A competing risks approach will be adopted to estimate comparative incidences to allow for the impact of mortality.

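### The aim promises a comparison of obesity risk between the three treatments, but the stated obesity analysis tests only against the general population and gives treatment groups only as stratified prevalences

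*Protocol article*

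**What the plan says.** The protocol article describes the role of obesity at three levels.

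- **Aim.** Under Aims and objectives the study is "to investigate the risks of gaining weight and developing obesity", together with cardiometabolic disease and death, "and to compare these risks between the three treatment modalities". The abstract (Methods and analysis) says the same: the study will "investigate the risk of obesity and risks of cardiometabolic conditions and death relative to the treatment".
- **Objective and outcome.** Under Primary objective, the effect of treatment type is tied to weight change. For obesity the comparator is different: "The post-treatment prevalence of obesity will also be evaluated and compared with that of the general population". The Outcomes section makes obesity prevalence after treatment part of the primary outcome, alongside weight change.
- **Analysis.** Under Prevalence of obesity: "The prevalence of obesity will be assessed in the entire cohort and stratified by the treatment group". Two effect measures follow, a BMI difference and a difference in obesity proportions. Then: "The effects will be tested with linear regression and logistic regression, respectively, in reference to the background population". The models adjust for age, are run by sex and use complete cases.

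**The concern.** A comparison of risk between treatments needs a contrast between treatments. Both obesity effect measures are defined with the survey population as reference, so neither is a contrast between ATD, radioiodine and thyroidectomy. What remains for that question is a set of prevalences by treatment group, with no planned estimate of the difference and no allowance for how patients came to be treated one way or another. The propensity model under Cardiometabolic risks and mortality lists aetiology, baseline fT4, deprivation, smoking and BMI status as candidate predictors of treatment. Differences in these would pass straight into the stratified prevalences.

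Two things are at stake. First, one half of the primary outcome would get a weaker between-treatment analysis than the secondary outcomes, which are inverse-propensity weighted. Second, readers who want to know whether one treatment carries more obesity would have to compare strata informally. The section on patient and public involvement shows that patients asked about radioiodine and weight in just this way.

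**Working it through.** The point is a missing contrast, and the article states no sample size, power or alpha for obesity, so there is no figure to reproduce. The check is whether any section supplies a between-treatment analysis of obesity.

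| Section | Outcome | Reference | Between-treatment contrast? |
|---|---|---|---|
| Natural history of weight changes | Weight, kg | ATD group | Yes, with Bonferroni for pairwise comparisons |
| Prevalence of obesity | BMI; obesity ≥30 kg/m² | Health Survey for England | None stated; prevalence by treatment stratum only |
| Cardiometabolic risks and mortality | Table 1 outcomes | Other treatment groups, propensity weighted | Yes, but obesity is not in Table 1 |
| Sensitivity to missed radioiodine record | Repeats all analyses | As in each analysis | Adds no new contrast |

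Step by step:

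1. The weight model does compare treatments. A mean difference in kilograms does not give the proportion of patients at or above 30 kg/m², because that also depends on height and on the starting BMI distribution.
2. The propensity-weighted Poisson and Cox models are stated for cardiometabolic outcomes and death. BMI status enters there only as a candidate covariate for the weights.
3. The obesity section fixes the type of model, the reference, the adjustment and the missing-data rule. None of these makes treatment the exposure.

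Hence, followed as written, the plan yields prevalence by treatment group and a comparison with the survey, but no between-treatment contrast that is tested or adjusted for treatment selection.

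**Illustration only.** Group sizes are assumed. The 32% and 37% are borrowed for scale from the earlier cohort of 1373 patients cited in the Introduction, where they are the figures for women and men, not for treatments.

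- Difference: 0.37 − 0.32 = 0.05, with 1000 and 5000 patients.
- Standard error: √(0.37×0.63/1000 + 0.32×0.68/5000) = √(0.0002331 + 0.0000435) = 0.01663.
- Two-sided alpha 0.05: power = Φ(0.05/0.01663 − 1.960) = Φ(1.046) ≈ 85%.
- Bonferroni for three pairs, alpha 0.05/3 = 0.0167, critical value 2.394: power = Φ(3.006 − 2.394) = Φ(0.612) ≈ 73%.
- With the pooled null standard error (pooled proportion 1970/6000 = 0.328, standard error 0.01627): Φ((0.05 − 2.394×0.01627)/0.01663) = Φ(0.664) ≈ 75%.
- With 500 instead of 1000 patients in the smaller group, the Bonferroni-level power is about 43–45%.

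The Bonferroni figures are the relevant ones, because the remedy adopts that rule. They describe an unweighted comparison; variable propensity weights would lower them.

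**The case against.** The strongest reply is that the specific objective and the analysis agree. The Primary objective assigns the between-treatment question to weight change and gives obesity only the general population as comparator, and the obesity section does that. This stands: the mismatch is between the broad aim (Aims and objectives, abstract) and a narrower objective and analysis. It is why narrowing the aim is an acceptable remedy. It does not remove the mismatch, since the aim as worded includes obesity among the risks to be compared.

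Second, a reader might infer that the study will give no information on obesity by treatment. The article does not support that: prevalences by treatment group will be reported. What is not stated is a tested or adjusted contrast.

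Third, a reader might infer that each treatment group will be tested separately against the survey, so that a large group could be significant and a small one not at the same true prevalence. That would be a real hazard, but the article does not say it will be done. Its wording fits separate fits per group, one model with a four-level factor (population and three treatments), or a comparison of the pooled cohort only. Probabilities of such discordant results belong to one unstated reading and to assumed group sizes, so the point does not rest on them.

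Fourth, the Confounding section promises adjustment of modelled outcomes for a wider covariate set. That holds in general, but the obesity section names only age and sex for its models and includes no model with treatment as exposure to which the wider set could apply.

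Last, this is a condensed article, and the full approved protocol or an analysis plan may hold more. That would excuse a missing detail. Here the article states the obesity analysis explicitly, and that analysis cannot meet the aim as worded.

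**Conclusion.** The concern holds in a limited form. The aim is to compare obesity risk between the three treatments; the stated obesity analysis compares BMI and obesity with the general population and, by treatment, offers only stratified prevalences. The conclusion rests on the text alone and on no assumed number. It is not a claim that obesity by treatment goes unreported, nor that the comparison with the survey is wrong: that comparison matches the Primary objective and is useful context.

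The size of the consequence cannot be derived from the article. On assumed sizes of 5000 and 1000 patients and prevalences of 32% and 37%, a direct test would have about 73–75% power at the Bonferroni level, so the missing analysis could be informative. With a smaller group of 500 it would be much less so (43–45%). It should be corrected, because the aim and the analysis of a primary outcome disagree and the remedy is cheap.

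**What to change.** Add a between-treatment analysis to the section Prevalence of obesity:

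- logistic regression for post-treatment obesity, and linear regression for post-treatment BMI, with treatment group as exposure and ATD as reference;
- the generalised propensity weights already planned under Cardiometabolic risks and mortality. BMI status is a candidate covariate there but is subject to the p<0.10 screen, so state that premorbid BMI is included regardless;
- pairwise estimates with confidence intervals, under the Bonferroni rule already set for weight;
- the Health Survey for England comparison kept as context, with a sentence that differences between strata in it are not evidence of a treatment difference.

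The alternative is to reword the aim in Aims and objectives and in the abstract, so that for obesity it covers only the comparison with the general population.

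The first option needs no new data source and no new weighting method. Its cost is a few lines of text and three more pairwise contrasts per effect measure, with the loss of power that their correction brings. The second costs only wording, but gives up the between-treatment question for obesity.
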